### **8.7 Follow-up of unresolved AEs**

All AEs should be followed up until they have been resolved, stabilized or returned to baseline status.

## **9 SAFETY EVALUATION**

Level 1: safe, no ADRs;

Level 2: relatively safe, treatment continues without any intervention;

Level 3: safety issues observed, but treatment can be continued after proper intervention;

Level 4: study termination due to ADRs.

## **10 DATA MANAGEMENT**

### **10.1 Collection and fulfillment of CRF**

The investigators fill in the 3-copy CRF of every patient enrolled in a complete, accurate, and timely manner. After the monitors review the completed CRF, the first copy of the CRF will be sent to the statisticians for data collection and management. Once the first copy of the CRF is submitted, the CRF will not be done any modification.

### **10.2 Data collection and management**

The statisticians are responsible for data collection and management. Data management will be performed via EpiData 3.0. To assure the accuracy of the data, two statisticians should record the data from the CRF independently. Once there are any queries about the CRF, the statisticians should fill in a data queries form (DQF), and send it to the monitors. Then the monitors require the investigators to resolve the queries as soon as possible. The statisticians will do the data modification according to the correspondence from the investigators. The statisticians could send another DQF if necessary.

### **10.3 Data Lock**

After confirming the accuracy of the database established from the CRF, the investigators, sponsor, statisticians will agree to lock the data. The locked database should not be done any modification. Any problems found after the data lock will be resolved in the procedure of statistical analysis.

## **11 STATISTICAL CONSIDERATIONS AND ANALYTICAL PLAN**

### **11.1 Selection of data sets**

#### **11.1.1 Efficacy analysis sets**

Full analysis set (FAS): includes all randomized patients and those without any evaluable follow-up data after randomization are excluded. For patients who did not complete the study according to the protocol, a last observation carried forward (LOCF) procedure was performed.

Per protocol set (PPS): includes all subjects in the FAS population who meet the study treatment compliance criteria and had no major protocol violations.

For primary outcome measures, statistical analyses will be performed separately in both FAS and PPS populations.

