#### **4.5.3 Withdrawal/dropout criteria**

- Those who did not fulfill the eligibility criteria but were included by mistake;
- Those who fulfilled the eligibility criteria but did not take any study drug after randomization;
- Those with poor compliance that might interfere with the efficacy and safety evaluation;

- Those who experienced serious AEs, complications or special physiological changes, making it inappropriate to continue with the trial;
- Individual cases that were unblinded prematurely;
- Those who discontinued the trial voluntarily;
- Those who used any disallowed concomitant medication, especially those that had an obvious effect on the study drug and might interfere with the efficacy and safety evaluation;
- Those who discontinued or lost to follow-up for any other reasons or died during the trial;
- Those with incomplete data that might interfere with the efficacy and safety evaluation.

For all withdrawal/dropout cases, the potential reasons must be recorded. Patients who experienced any AE during the trial must be included in the statistical analysis of adverse drug reactions. Those who have taken the study drug for at least 1 week should be included in the statistical analysis of drug efficacy.

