#### **4.5.5 Criteria for subject discontinuation**

- Any allergic reaction or AE occurs such that continued participation in the study would not be in the best interest of the subject at the discretion of the treating physician;
- Worsening of clinical conditions occurs such that continued participation in the study would not be in the best interest of the subject at the discretion of the treating physician; considered as ineffective cases;
- Subjects are free to withdraw from participation in the study at any time upon

request.

In any case, every effort must be made to determine why patients discontinued the study treatment prematurely, which may include but are not limited to poor confidence in efficacy, occurrence of AEs, SAEs, or other serious complications, worsening of symptoms such that emergent intervention is required. As for those who withdrew from participation in the study or lost to follow-up, it is essential to investigate the potential reasons via telephone or mail. Investigators should record in detail when and how the last dose was administered, the efficacy and safety parameters at and after discontinuation, the relationship between discontinuation or withdrawal and the study drug, and the potential impact of discontinuation cases on the final conclusion of the study. Moreover, case report form (CRF) of withdrawal/dropout cases should also be completed and their original data should also be documented and stored in a secure manner.

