### 6.2 Efficacy parameters

The primary efficacy endpoint of this study is:

- Proportions of patients who were angina-free.

Angina-free was defined as the responses of patients' anginal symptoms were "none" on the Quantification Score of Angina Pectoris (see page 19 for details) including three dimensions (attack frequency, severity and duration of angina) over the 20-weeks treatment phase. The Quantification Score of Angina Pectoris comprising questions investigating the patients' anginal symptoms was administered by the physician in charge of the study at 2, 4, 6, 8 and 20 weeks in each center.

- Proportion of effective electrocardiogram (ECG) improvement.

The effective ECG improvement was defined as a standard 12-lead ECG returns to normal(or within the normal range) according to the International Society and Federation of Cardiology/World Health Organization after 20-weeks long term treatment. The ECG was performed at 0,8, and 20 weeks during treatment.

Secondary efficacy endpoints are:

- Change from baseline in weekly average frequency of self-reported angina episode over the 20-weeks treatment phase.
- Weekly average nitroglycerin consumption rate at week 8 and week 20.

Throughout the study, patients recorded the occurrence of anginal attacks and the number of nitroglycerin use on diary cards and the study staff at each clinical site reviewed the angina and nitroglycerin use cards with the patient at each study visit(2, 4, 6, 8 and 20 weeks) to ensure accuracy.

- Change from baseline in 5 dimensions of the Seattle Angina Questionnaire (SAQ) and the proportions of patients who were clinical significance at week 8 and week 20.

The SAQ is a disease-specific functional status measure that was developed to quantify the physical and emotional effects of CAD[6].Each SAQ dimension (anginal frequency, physical limitation, anginal stability, disease perception, and treatment satisfaction) was scored on a scale of 0 to 100 and the clinical significance was defined as a difference of 8 points or more on the physical-limitation scale, 25 or more on the angina-stability scale, 20 or more on the angina-frequency scale, 12 or more on the treatment-satisfaction scale, and 16 or more on the quality-of-life scale[7].Patients will complete the SAQ at 0,8, and 20 weeks.

- Change from baseline in the blood stasis syndrome and the proportion of patients who had significant syndrome improvement.

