### **8.6 Opening and handling of emergency envelopes**

The emergency envelope provided along with each test drug in its package should only be opened in case of a serious complication or a serious adverse event, which is called emergency unblinding. Once unblinded, the patient should be withdrawn from the study and regarded as a dropout case. Information about when, where and why the emergency unblinding occurs as well as each personnel's signature should also be documented.

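### LOCF for every non-completer can score an early leaver as a 20-week responder, and for patients stopped for worsening it can conflict with section 4.5.5

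*Protocol*

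**What the plan says.** Protocol section 11.1.1 defines the full analysis set (FAS) as one that "includes all randomized patients and those without any evaluable follow-up data after randomization are excluded", and then sets the missing-data rule: "For patients who did not complete the study according to the protocol, a last observation carried forward (LOCF) procedure was performed". The rule does not depend on why the patient left.

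Both primary endpoints in section 6.2 are tied to 20 weeks. Angina-free requires no angina on three dimensions: "attack frequency, severity and duration of angina) over the 20-weeks treatment phase". The score is "administered by the physician in charge of the study at 2, 4, 6, 8 and 20 weeks in each center". ECG response means a normal tracing after 20 weeks of treatment, with ECGs at weeks 0, 8 and 20 only. The flowchart in section 15 shows the same visits.

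Three other sections deal with patients who leave:

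- Section 4.5.5, on patients discontinued because their condition worsens: "at the discretion of the treating physician; considered as ineffective cases".
- Section 4.5.3: "Those who have taken the study drug for at least 1 week should be included in the statistical analysis of drug efficacy".
- Section 8.6, on emergency unblinding: "Once unblinded, the patient should be withdrawn from the study and regarded as a dropout case".

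**The concern.** A responder endpoint defined over or after 20 weeks should not be met on a value from week 2, 4, 6 or 8 followed by departure, yet 11.1.1 allows this. The listed ways of leaving (4.5.3 and 8.6) include serious adverse events, unblinding, disallowed medication, death and loss to follow-up, and none of them changes the carried value.

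For one group the protocol also gives two answers. A patient stopped for worsening is ineffective under 4.5.5, but may be a responder under 11.1.1 if the last value used was favourable. Neither section says which rule prevails, so the choice could be made at analysis, on a primary endpoint.

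The set of patients analysed is in doubt as well, because 4.5.3 and 11.1.1 admit patients to the efficacy analysis on different conditions.

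**Working it through.** **The rules applied to individual patients**

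| Patient | Under 11.1.1 | Under the other text |
|---|---|---|
| No angina at week 8, then lost | Angina-free; value carried 20 − 8 = 12 weeks, or 12/20 = 60% of treatment | 6.2 asks about the whole 20-week phase |
| No angina at week 2, then leaves | Angina-free; value carried 20 − 2 = 18 weeks | As above |
| Normal week-8 ECG, then leaves | ECG responder | 6.2 asks for a normal ECG after 20 weeks |
| No angina at week 8, then stopped for worsening, no later score used | Angina-free | 4.5.5: ineffective |
| As above, but a failing score at discontinuation is used | Not angina-free | 4.5.5: ineffective, so no conflict on this endpoint |
| Leaves on day 10 with no assessment | Outside the FAS | 4.5.3: in the efficacy analysis |

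The last row arises because the first follow-up visit is at week 2, while 4.5.3 asks for only one week of drug.

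**Inputs for the size**

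- The plan gives no figure for this effect and no dropout rate.
- Section 3.2 raises 465 to 576 for dropout and site blocking together. Dropout is therefore at most 1 − 465/576 = 19.3%.
- The re-estimation text in 3.2 sets 736 patients (736/2 = 368 per arm) and mentions a low dropout rate.
- Completer rates are the design values in 3.2: p = 30% (trial) and 20% (control).
- Assumed: dropout d from 5% to 19.3%, and a share q of 10% to 30% of non-completers whose last observation is a success. All non-completers are taken to have some follow-up, and so to be in the FAS.

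**Effect on one arm's rate**

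LOCF rate = p(1 − d) + dq. Non-responder rate = p(1 − d). The gap is dq.

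| d | Gap at q = 10% | Gap at q = 30% | Patients per arm (368 × d × q) |
|---|---|---|---|
| 5% | 0.5 points | 1.5 points | 1.8 to 5.5 |
| 10% | 1.0 | 3.0 | 3.7 to 11.0 |
| 19.3% | 1.9 | 5.8 | 7.1 to 21.3 |

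**Effect on the treatment difference at d = 19.3% in both arms**

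- Non-responder counting: 24.2% − 16.1% = 8.1 points.
- LOCF with equal q in both arms: also 8.1 points.
- LOCF with q = 30% trial, 20% control: 30.0% − 20.0% = 10.0 points.
- LOCF with q = 20% trial, 30% control: 28.1% − 21.9% = 6.1 points (from unrounded rates).

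The sign of the shift depends on q in each arm, which the protocol does not give.

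**Power under non-responder counting**

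With 368 per arm and two-sided 5%, power = Φ[(Δ − 1.96·SE₀)/SE₁], where SE₀ uses the pooled rate and SE₁ the separate rates. Dropout is equal in both arms.

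| d | Rates | Difference | Power |
|---|---|---|---|
| 0 | 30.0% vs 20.0% | 10.0 points | 88.1% |
| 5% | 28.5% vs 19.0% | 9.5 | 85.9% |
| 10% | 27.0% vs 18.0% | 9.0 | 83.4% |
| 19.3% | 24.2% vs 16.1% | 8.1 | 78.0% |

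**The case against.** The strongest objection is that LOCF need not bias the comparison and that non-responder counting can. A reader might infer that unequal dropout under LOCF creates a false effect. Take 25% success in both arms, among completers and at the leavers' last visit, with dropout of 20% and 10%. LOCF then credits 5.0 and 2.5 points to leavers, an apparent gap of 2.5. But completers contribute 0.80 × 25% = 20.0 and 0.90 × 25% = 22.5 points, so both arms total 25% and the gap vanishes. Counting leavers as failures gives 20.0% against 22.5%. This objection stands: the documents do not support a claim that LOCF favours either product, and either rule can mislead if dropout differs by arm.

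A reader might also take the conflict with 4.5.5 to cover every dropout. It does not, because 4.5.5 speaks only of worsening. It also asks for efficacy parameters at and after discontinuation, so a failing angina score may well be the last observation. The conflict remains where no such score is recorded or used, or where a normal week-8 ECG is carried. Ineffective is also a category of the section 7 response scale, not of the primary endpoints, but it cannot sensibly coexist with angina-free status or a normalised ECG.

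The ECG problem is confined to week 8. Before that only baseline exists, and entry (4.5.1) requires ischaemic ECG changes or a positive exercise test, so a carried baseline would usually be a failure.

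The protocol does have partial safeguards. Section 11.1.1 analyses the primary outcomes in both FAS and per-protocol set, and 11.2 compares dropout between arms. Neither sets an outcome for non-completers. A separate statistical plan may add sensitivity analyses, but the protocol itself fixes LOCF.

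**Conclusion.** The point holds in three parts.

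- LOCF as written can give a success on a 20-week primary endpoint to a patient not seen at week 20. For dropouts other than those stopped for worsening, this is a mismatch with the endpoint definition in 6.2 and not a contradiction of 4.5.5.
- For patients stopped for worsening, 11.1.1 and 4.5.5 conflict whenever a failing value at discontinuation is not recorded and used.
- The efficacy population is stated two ways, which differ for patients who leave before the first assessment.

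The size is about 0.5 to 5.8 points on an arm's response rate, or roughly 2 to 21 patients of 368, relative to non-responder counting. This rests on the assumed dropout and last-visit success. The 19.3% is a ceiling because it includes site blocking, and the remark on low dropout in 3.2 points to the lower end. A reader might treat 19% as the planned dropout rate, or suppose that most leavers are treatment failures. The protocol gives no rate and no counts by reason, so neither follows. The direction of any bias in the treatment difference cannot be determined.

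**What to change.** In section 11.1.1, state for both primary endpoints in the FAS that:

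- patients stopped for worsening are non-responders, in line with 4.5.5;
- patients without a week-20 assessment are non-responders in the primary analysis;
- LOCF is kept as a sensitivity analysis, since either rule can mislead if dropout differs by arm.

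Reconcile the one-week condition in 4.5.3 with the FAS definition, so that one statement governs who enters the efficacy analysis.

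This is a change of wording only, with no new data. It makes leaving early part of the endpoint, which is a choice of what to estimate and should be stated as such. The price is lower response rates, a smaller difference and some power: with 368 per arm and completer rates of 30% and 20%, about 86% at 5% dropout, 83% at 10% and 78% at the 19.3% ceiling, against 88% with no dropout.

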#### **11.1.2 Safety analysis set**

The safety analysis set (SS) is defined as a subset of subjects who took at least 1 dose of study drug after randomization.

#### **11.2 Dynamic statistical plan**

One interim analyses will be conducted under blinding conditions after 1/2 of the total number of cases have completed the trial.

Statisticians and principal investigators are responsible for drafting a written plan for statistical analysis according to the study protocol. It includes the number of included, excluded or withdrawal patients, the demographic and baseline characteristics of included patients, treatment compliance, efficacy analysis and safety analysis.

Qualitative data will be described with absolute and relative (proportion or percentage) values; and quantitative data will be summarized with mean, standard deviation, maximum, minimum, and median.

Paired t-test will be used for comparison before and after treatment within a treatment group. In analysis of variance (ANOVA) for multiple comparisons within a group, if the variances are assumed to be equal, then Student-Newman-Keuls (SNK) significance test will be used for pairwise comparison; if the variances are not assumed to be equal, then non-parametric test will be applied. Two-samples t-test will be used for comparison between treatment groups. Fourfold table will be displayed for comparison of categorical parameters: Chi-squared test for nominal categorical data and rank sum test for ordinal categorical data. Also, the analysis of covariance (ANCOVA) can be used to control for potential confounding variables.

All *P* values are two-side. Statistical significant level is set to be 0.05.

For between-group comparisons, chi-square test, Fisher's exact test, Wilcoxon rank test or Cochran-Mantel-Haenszel (CMH)  $\chi^2$  test may be used for qualitative data; while t-test, ANOVA, Wilcoxon rank test or ANCOVA may be applied for quantitative data.

**Baseline analysis:** Demographic and baseline characteristics will be reported for each subject. Comparisons between the treatment groups will be conducted using ANOVA or

Chi-square test to assess the degree to which comparability of randomization can be achieved.

**Dropout analysis:** The overall dropout rate and the dropout rate due to AEs will be compared between the treatment groups by using Chi-square test.

**Efficacy analysis:** The effect of different study sites on efficacy parameters will be considered and analyzed.

**Dynamic change of TCM syndrome (phenotypic group):** The method of Multidimensional Scaling Analysis (MDS) will be used to investigate the changing tendency of the phenotypic group at different time points in different treatment groups. Different dimensionality values of any patients at different time points make up a vector which is called control vector; and the maximum values of the quantification score of six phenotypes make up another vector, which is called standard vector. The included angle cosine method commonly used in Similarity Degree Analysis (SDA) is adopted to analyze the similarity degree of different patients at different time points. Nonlinear mixed effect model (NONMEM) is built to analyze the nonlinear relationship between the TCM syndrome (phenotypic group) and observation time points, also to identify the cutoff point in the dynamic change of the TCM syndrome (phenotypic group).

**Safety analysis:** Safety will be evaluated by tabulations of adverse events and will be presented with descriptive statistics at baseline and follow-up visits for each treatment group. Adverse event incidence rates will be summarized by system organ class, preferred term, and severity of the adverse event. All information pertaining to adverse events noted during the study will be listed by subject, preferred term, system organ class, date of onset, date of resolution, severity, and relationship to study drug.

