### 4.4 Quantification score of TCM syndrome (phenotypic group)[3]

#### 4.4.1 Scoring system

(1) Chest pain: stabbing, gripping, and fixed pain, which radiates to shoulder, back or the medial side of the arm

0 points: none;

2 points: relieved with rest, daily activities not being affected;

4 points: relieved with medication, daily activities not being affected after remission;

6 points: frequent attacks, daily activities being affected (e.g. putting on clothes, eating, walking, or even making a bowel movement may induce symptoms).

(2) Choking sensation in the chest

0 point: none;

1 point: mild chest distress occurs occasionally, which may disappear without any

intervention;

2 points: frequent chest distress, sighing respiration at times, but daily activities not being affected;

3 points: persistent chest suffocation and sighing respiration, daily activities being affected.

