### (3) Palpitation

0 point: none;

1 point: mild palpitation occurs occasionally, which may disappear without any intervention;

2 points: obvious palpitation occurs sometimes, which may last for a relatively long period, but daily activities can be continued;

3 points: persistent palpitation, which may present even at rest, daily activities being affected.

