### **7.3 Evaluation of syndrome changes**

The evaluation of syndrome changes should be based on the quantification score of the TCM syndrome:

- Markedly effective: clinical signs and symptoms have been greatly improved, and decrease in syndrome score  $\geq 70\%$ ;
- Effective: clinical signs and symptoms have been somewhat improved, and decrease in syndrome score  $\geq 30\%$  but  $< 70\%$ .
- Ineffective: clinical signs and symptoms remain unchanged, and decrease in syndrome score  $< 30\%$ ;
- Worsening: clinical signs and symptoms become worse, and decrease in syndrome score  $< 0$ .

The dynamic changes in the phenotypic group should also be assessed.

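### The cosine similarity planned to follow change in blood stasis syndrome ignores overall severity and has no value at full recovery, so it is not a reliable measure of improvement

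*Protocol*

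**What the plan says.** Protocol section 7.3 grades syndrome response by the percentage fall in the syndrome score and then adds: "The dynamic changes in the phenotypic group should also be assessed". Section 11.2, under the heading on dynamic change of the TCM syndrome, gives the method. The patient's side of the comparison is defined as follows: "Different dimensionality values of any patients at different time points make up a vector which is called control vector". The reference is defined as follows: "the maximum values of the quantification score of six phenotypes make up another vector, which is called standard vector". The two are compared by the cosine of the angle between them: "The included angle cosine method commonly used in Similarity Degree Analysis (SDA) is adopted". Its stated use is to judge how similar patients are across visits. The same paragraph also plans multidimensional scaling (MDS) by treatment group and a nonlinear mixed effect model of the syndrome over time. It gives no rule for a patient whose six items are all 0, and it pairs the cosine with no measure of size.

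The item maxima are in section 4.4.1. Chest pain runs to 6 ("6 points: frequent attacks, daily activities being affected"). Choking sensation, palpitation and lips each run to 3. Tongue runs to 2 and pulse to 1. Every item has a 0 level.

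**The concern.** The reference vector is the worst possible state, so a reader will take a falling cosine as recovery and a steady or rising one as no response or worsening. A cosine does not support that reading. It compares direction only: two patients with the same profile but very different severity score alike, and a patient may move closer to the reference simply because the remaining mild symptoms happen to be in the same proportions as the maxima. The best outcome on the scale, no symptom at all, has no direction and therefore no cosine. At stake is a supplementary account of how the syndrome evolves. It could disagree with the score-based endpoints for the same patients, and it would have missing values exactly where treatment worked best.

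**Working it through.** The protocol states no figure for this analysis, so there is none to reproduce. The check applies the stated formula to the protocol's own scale.

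**Inputs**
- Reference vector from the maxima in section 4.4.1, in the order chest pain, choking, palpitation, lips, tongue, pulse: s = (6,3,3,3,2,1), total 18.
- |s|² = 36+9+9+9+4+1 = 68, so |s| = 8.246.
- Patient vector v: the six item scores at one visit. This is an assumption, taken up under the objection.
- Formula: cos = (v·s)/(|v||s|).
- Severity bands from section 4.4.2: mild up to 6, moderate 6 to 10, severe 11 or more.
- Entry rule from section 4.1.2: chest pain, at least two of the three accompanying symptoms, and both the tongue and pulse signs present.

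**Size is ignored**
- (6,3,3,3,0,0), total 15, severe: 63/(7.937 × 8.246) = 0.9625.
- (4,2,2,2,0,0), total 10, moderate: 0.9625.
- (2,1,1,1,0,0), total 5, mild: 21/(2.646 × 8.246) = 0.9625.

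These three have no tongue or pulse sign, so none can be an entry profile. They can occur at follow-up visits.

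**Full recovery**
- (0,0,0,0,0,0): 0/0. It is the only undefined vector among the 4×4×4×4×3×2 = 1,536 possible ones.

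**Change from profiles that meet the entry rule**

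| From | To | Total | Fall | Cosine |
|---|---|---|---|---|
| (6,3,3,3,2,1) | (2,1,1,1,0,0) | 18 to 5 | 72% | 1.000 to 0.9625 |
| (2,3,3,3,2,1) | (2,1,1,1,0,0) | 14 to 5 | 64% | 0.889 to 0.9625 |
| (2,3,3,1,2,1) | (2,1,1,1,1,0) | 12 to 6 | 50% | 0.871 to 0.986 |

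In the second row, v·s = 44 and |v| = 6 at the start, so the cosine is 44/(6 × 8.246) = 0.889. The patient goes from severe to mild while the cosine moves towards the most severe reference. The first row meets the 70% score threshold of the best response grade in section 7.3, yet the cosine moves by less than 0.04.

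**How often this can happen on the scale**

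The entry rule admits 3 × 54 × 2 × 1 = 324 profiles (chest pain; accompanying symptoms; tongue; pulse). Each was paired with every vector that is no higher on any item and lower in total. Pairs are counted equally, so the shares describe the scale and do not predict patient frequencies.

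- All 87,156 improving pairs: the cosine falls in 95.3%, rises in 4.3%, ties in 17 pairs, and is undefined in 324 (0.4%).
- Pairs with a fall in total of at least 70% (14,224): it falls in 97.7%. Nearly all the rest are the 324 undefined full recoveries (2.3%).
- Pairs in which the same symptoms persist but are milder (5,508): it falls in 75.2% and rises in 24.7%, with a median change of only -0.02.

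The cosine falls mainly because symptoms disappear and the profile changes. When symptoms ease without disappearing, it is weak and often points the wrong way.

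**The case against.** The strongest reply is that the cosine does respond. A reader might infer from the formula that it cannot show improvement at all, or that response is invisible to it. The enumeration contradicts that: it falls in 95.3% of improving pairs. An exactly proportional improvement from an entry profile is also impossible short of full recovery, because pulse is 1 at entry and can only go to 0. The exact ties listed above lie between other states.

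A reader might also infer that the cosine is the protocol's comparison of the two arms and would distort the estimated treatment effect. The text does not say so. The words on different treatment groups belong to the MDS sentence, the cosine sentence speaks only of patients and time points, and the mixed effect model does not name the cosine as its response. Nor does the protocol say that recovered patients are dropped. Handling of an all-zero vector may be settled in a statistical plan that is not shown.

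Severity is measured elsewhere: section 6.2 makes change in the syndrome score, and the proportion with a fall of at least 70%, secondary endpoints.

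Finally, the definition of the patient's vector follows directly on the MDS sentence and could mean MDS coordinates. The numbers and the zero-vector argument would then need restating. That reading brings its own difficulty, because MDS coordinates do not share axes with a reference made of raw score maxima, so the definition would still need correction.

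All of this limits the point but does not remove it. The formula itself is fixed in the protocol, and it is poorly suited to the stated aim of following dynamic change.

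**Conclusion.** The point holds in a limited form. As a measure of change in the syndrome, the cosine against the maximum-score vector is unreliable: it is blind to overall severity, it can barely move or rise during clear improvement, and it is undefined at full recovery. If visits with all items at 0 were left out, the best responders would be lost, and more of them in whichever arm had more full recoveries.

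The practical weight is small. The analysis is supplementary, and the primary endpoints, the sample size and the score-based syndrome endpoints do not depend on it. The conclusion assumes that the patient's vector is the six item scores at a visit, and the percentages weight every possible pair of score profiles equally.

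**What to change.** In the dynamic-change paragraph of section 11.2:

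1. State that the patient's vector is the six item scores of section 4.4.1 at each visit.
2. For change over time, use a measure that keeps size and is defined at zero, and model it over visits by arm. Three options are the total score divided by 18, the projection v·s/|s|², or the distance from the all-zero vector. For the patient going from 14 to 5 points, the first falls from 14/18 = 0.78 to 5/18 = 0.28, and the second from 44/68 = 0.65 to 21/68 = 0.31. All three equal 0 at full recovery. The first is the existing syndrome score rescaled, so it cannot contradict the secondary endpoint.
3. Keep the cosine, if wanted, only as a description of symptom pattern among patients with a non-zero score, and report the number with all-zero scores by arm at each visit.

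The cost is a changed formula and a few sentences. The flowchart in section 15 already collects the syndrome score at every visit, so no new data are needed.
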